### Discussion

Psychological distress associated with cancer diagnosis and treatment is high. Yet, psycho-oncological support is often lacking –due to barriers on the patients’ side or to insufficient resources on the providers’ side [15]. Online-interventions with regular psychologist-contact (minimal-contact) -already established in several psychological disorders- might reduce this gap. In our prospective, randomized controlled study we assess the first minimal-contact, online stress management program for German-speaking, newly diagnosed cancer patients.

Our study will yield information on the efficacy of the intervention with respect to quality of life and stress/anxiety. In addition, it will show whether cancer patients are ready to use new technologies to further increase the range of treatment options at their disposal, and -even more importantly- whether patients who are in need of support but slip through the net of the current system can be reached. Conversely, the time- (and indirectly the cost-) effectiveness of administering support in a minimal-contact online intervention will be assessed from the providers’ perspective – an outcome with important implications for the health care system.

On a different level, the contribution of various and novel recruitment strategies (flyers, “conventional face-to-face”, internet links, Google Ads, Facebook Ads, You tube) will be described allowing for conclusions for future online study portals.

One of the limitations of the study is the heterogeneity of newly diagnosed cancer patients with respect to tumor type, treatment type and treatment strategies (curative, palliative). However, the distress of a new cancer diagnosis is their common denominator, and a stratification factor. Also, since this is the first online stress management program for newly diagnosed cancer patients, we deliberately aim at reaching a broad population to avoid missing a small but important group of patients with potential benefit from this intervention. The results of this study will allow characterizing the patient population(s) with respect to age, sex, diagnosis and treatment that will then be studied more specifically in follow-up trials. Our trial represents a first step in expanding the much-needed psychological support for newly diagnosed cancer patients towards the promising approaches that come with new technical possibilities which have become integral part of our lives.

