**Methods/design:**

In a prospective, wait-list controlled trial 120 newly diagnosed cancer patients will be included within 12 weeks of starting anti-cancer treatment and randomized between an immediate (intervention group) or delayed (control group) 8-week, web-based intervention. The intervention consists of eight modules with weekly written feedback by a psychologist (“minimal-contact”) based on well-established stress management manuals including downloadable audio-files and exercises. The aim of this study is to evaluate efficacy in terms of improvement in quality of life (FACT-F), as well as decrease in anxiety and depression (HADS), as compared to patients in the wait-list control group. A sample size of 120 patients allows demonstrating a clinically relevant difference of nine points in the FACT score after the intervention (T2) with a two-sided alpha of 0.05 and 80 % power. As this is the first online stress management intervention for German-speaking cancer patients, more descriptive outcomes are equally important to further refine the group of patients with the largest potential for benefit who then will be targeted more specifically in future trials. These descriptive endpoints include: patients’ characteristics (type of cancer, type of treatment, socio-demographic factors), dropout rate and dropout reasons, adherence and satisfaction with the program.

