## Background

### Impact of cancer on mental health

Every second cancer patient suffers from clinically relevant psychosocial distress [1]. Psychosocial distress encompasses emotional lability, rearranging of roles and responsibilities, changing of future plans, fear of recurrence, depression and anxiety and is associated with decreased quality of life [2–4]. In addition, high levels of distress lead to reduced compliance with treatment and more side effects [5, 6]. Conversely, side effects of cancer treatment like fatigue, nausea and pain may trigger distress and, therefore, impact psychological adjustment.

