## Methods/design

In a prospective randomized controlled intervention study (Fig. 1) patients are randomized 1:1 (mixed randomization scheme using unequal block randomization) between the intervention group and the wait-list control group. Patients are stratified according to baseline stress level (distress thermometer ≥ *vs* < 5 [27]). A total of 120 newly diagnosed adult (>18 years) cancer patients who started first-line treatment (either systemic treatment - including chemotherapy, hormonal treatment or targeted therapy - or radiotherapy) no longer than 12 weeks earlier are included after giving informed consent. Patients who undergo treatment for a first relapse of a tumor previously treated with curative intent are also eligible. Patients are required to read and write in German, have internet-access as well as basic computer skills.

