### Statistical analyses and sample size calculation

Based on previous studies [43] including recent data on cancer patients [44], a difference of nine points in the FACT score is both, clinically significant and realistic. In order to demonstrate a 9-point difference between baseline and T2 (after 8 weeks) in the intervention group with a statistical power of 0.80 at a significance level of 0.05 (two-sided), 60 participants are needed in each of the two conditions. We assume normally distributed data in both groups with a standard deviation of ±18 [45]. Data preparation of all continuous dependent variables will include tests for normality, homogeneity of variances, and examination of outliers. If not normally distributed, variables will be subjected to adequate transformation. Intent-to-treat samples will be used to analyze data. The choice of statistical approach depends on the amount of missing data at T2 and T3. If less than 12 % of data are missing, the Last Observation Carried Forward (LOCF) method will be applied to estimate effects. Then, the outcome will be computed with an analysis of covariance (ANCOVA), using the pre-scores as a covariate and the post-scores as the dependent variable. If more than 12 % of data are missing, we will use linear mixed models. This method is recommended for intent-to-treat-analyses with a high amount of dropouts due to its potential to reduce bias caused by missing data. Regression analyses will be used to identify predictors of treatment outcome.

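### The T2 model names no background-treatment covariate and the distress stratum does not balance treatment, so a modest gain in precision is forgone

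*Protocol article*

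**What the plan says.** All places are in the protocol article.

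- **Who enters.** Methods/design describes patients starting first-line treatment: "either systemic treatment - including chemotherapy, hormonal treatment or targeted therapy - or radiotherapy) no longer than 12 weeks earlier are included". Treatment for a first relapse is also allowed. Assessments and Discussion show that curative and palliative settings both occur.
- **Endpoint.** Efficacy outcomes makes FACT quality of life, including fatigue, at T2 the main outcome.
- **Link between treatment and outcome.** The background section on mental health says that "side effects of cancer treatment like fatigue, nausea and pain may trigger distress". It gives no size.
- **Randomisation.** Methods/design names one stratification factor, the baseline distress thermometer at 5 or above versus below 5.
- **Analysis.** Statistical analyses and sample size calculation specifies an ANCOVA "using the pre-scores as a covariate and the post-scores as the dependent variable", or linear mixed models if more data are missing. No other covariate is named for either. A separate regression is planned to look for predictors of outcome.
- **Acknowledged limitation.** The Discussion lists tumour type, treatment type and treatment intent as sources of heterogeneity, then continues: "However, the distress of a new cancer diagnosis is their common denominator, and a stratification factor".
- **Data at hand.** Assessments lists past and current cancer treatments, with setting, in the medical history taken at T1.

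**The concern.** Entry can fall from 0 to 12 weeks after treatment start, so at T2 patients are roughly 8 to 20 weeks into chemotherapy, hormonal treatment, targeted therapy or radiotherapy. Two patients with the same FACT score at T1 may have different expected courses over the next 8 weeks, depending on what treatment they receive and with what intent. The pre-score records where each patient stands at T1, not that expected course.

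The Discussion meets this heterogeneity with the distress stratum. Balance on a distress score above or below 5 says nothing about balance on treatment type or setting. The one model that could take up those factors names only the pre-score, although both are collected at baseline.

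Two things are at stake. Variance that could be explained stays in the error term. And if the arms differ by chance in treatment mix, there is no prespecified adjustment; one added after the imbalance has been seen would be open to challenge.

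**Working it through.** **1. The plan's own figure.** The inputs are in the sample size section: "a difference of nine points in the FACT score is both, clinically significant and realistic", "with a standard deviation of ±18", and "with a statistical power of 0.80 at a significance level of 0.05 (two-sided), 60 participants are needed in each of the two conditions". I treat this as a two-arm comparison at T2, as the abstract does ("A sample size of 120 patients allows demonstrating a clinically relevant difference of nine points in the FACT score after the intervention (T2").

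- n per arm = 2 × 18² × (1.960 + 0.842)² / 9² = 62.8, so 63 (64 with the t distribution), not 60.
- SE at 60 per arm = 18 × √(2/60) = 3.29. Power = Φ(9/3.29 − 1.96) = 78.2 % (77.5 % with the t distribution).

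The small shortfall against 60 per arm is a separate matter. Here 78.2 % is only the reference value.

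**2. Precision from added covariates.** The documents give no prognostic strength for treatment, so the share of residual variance explained (R²) is an assumption. The SE is multiplied by √(1 − R²).

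| Assumed R² | SE ratio | Residual SD | Power at 60 per arm | n per arm for 80 % |
|---|---|---|---|---|
| 0 | 1.000 | 18.00 | 78.2 % | 63 |
| 0.02 | 0.990 | 17.82 | 79.0 % | 62 |
| 0.05 | 0.975 | 17.54 | 80.2 % | 60 |
| 0.10 | 0.949 | 17.08 | 82.3 % | 57 |

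If the pre-score already correlates 0.5 with the T2 score (assumed; the documents give no value), the starting power is 88.5 % and the same three R² values give 89.1 %, 90.1 % and 91.5 %.

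The table ignores the cost of estimating the covariates. With 120 − 3 = 117 residual degrees of freedom after intercept, arm and pre-score, each covariate costs roughly 1/117 = 0.9 % in variance. Two cost about 1.7 %, which nearly cancels the gain at R² = 0.02 and leaves most of it at 0.05 to 0.10.

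**3. Chance imbalance.** This uses simple binomial allocation, 60 per arm, and a treatment category held by half the patients.

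- SD of the between-arm difference in proportion = √(2 × 0.25/60) = 9.1 percentage points.
- Probability of a difference of at least 10 points: 32 %. At least 15 points: 12 %.

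**4. What such an imbalance would do, on the same assumptions as step 2.** A half-and-half factor with effect d contributes 0.25 × d² to a variance of 18² = 324.

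- R² = 0.02: d = √(0.02 × 324/0.25) = 5.1 points.
- R² = 0.10: d = √(0.10 × 324/0.25) = 11.4 points.
- At one SD of imbalance (0.091) the arm difference moves by 0.5 to 1.0 points. At a 15-point imbalance it moves by 0.8 to 1.7 points. The SE is 3.29 and the target is 9.

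Steps 2 and 4 describe the same variance component in two ways, so the effects must not be added.

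**The case against.** **A condensed article may leave covariates to a fuller plan.** Extra covariates are commonly listed in an analysis plan, and the article does not say that none will be used. This lowers the weight of the point. But the article does fix a model and name its covariate, and its stated answer to treatment heterogeneity is stratification on something else. Improving that stated model is a fair request.

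**Chance imbalance is not an error.** This stands. Under randomisation the standard error and p-value already cover it. A reader might infer that an uneven treatment mix biases the T2 comparison or inflates the type I error; neither follows.

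**The strength of the treatment effect is unknown.** This also stands. A reader might infer that background treatment drives the endpoint. The background section says only that side effects may trigger distress, and no passage gives a figure for FACT at T2. The pre-score is also taken after treatment has started, so it absorbs whatever is already visible at T1. Only differential change over the next 8 weeks remains.

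**Large shifts can be constructed.** An 18-point imbalance (1.96 × 9.1) with a 15-point difference in course gives 0.18 × 15 = 2.7 points, or 30 % of the 9-point target. But d = 15 implies 0.25 × 225/324 = 17.4 % of variance, beyond the 2 to 10 % assumed here, and the imbalance is at the edge of its 95 % range. The documents support neither value.

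**The Discussion may not claim that the stratum balances treatment.** Fair: it can be read as saying that distress is what these patients share, and it goes on to justify broad inclusion. It still offers nothing that deals with treatment in the comparison. The planned predictor regression is not an adjustment of it.

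**Conclusion.** The point holds as a recommended improvement, not as a flaw that invalidates the analysis. Treatment type and intent vary by design, are acknowledged as a limitation, are collected at T1, and are neither balanced by the single stratum nor named in the T2 model. The baseline-adjusted ANCOVA remains a valid comparison without them.

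The loss is modest. The standard error is about 1 to 5 % larger than it need be, and power is 78.2 % rather than 79.0 to 82.3 %. This assumes that the two factors explain 2 to 10 % of residual variance and uses a two-sample z calculation with SD 18 and 60 per arm. At the low end the degrees of freedom used cancel most of the gain. The further benefit is an agreed adjustment already in place should the arms differ visibly in treatment mix.

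**What to change.** In Statistical analyses and sample size calculation, state before any T2 data are examined by arm that the primary T2 model, whether ANCOVA or mixed model, includes:

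- the pre-score;
- the randomisation stratum (distress thermometer at 5 or above versus below), which is also not named in the model at present;
- current anti-cancer treatment type at T1, with a coding rule for combined treatments, for example any chemotherapy versus none, since combinations are not excluded;
- curative versus palliative setting at T1.

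Add weeks since treatment start only if the start date is recorded. Assessments lists time since diagnosis and the treatments, but not that date, and the 12-week entry limit does not show that it is stored. Use T1 values only, not changes after randomisation. In the mixed model, let the covariates act on the T2 visit (covariate-by-visit terms). Further stratification cells are not needed at 120 patients.

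In the Discussion, refer to this adjustment alongside the distress stratum where treatment heterogeneity is named.

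The cost is one sentence in each place and, with binary coding, three further degrees of freedom out of 120 patients. Treatment type and setting need no new data. At the date in Trial status, 80 of the 120 patients had been recruited, so the change could still be made before recruitment closed.

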### Trial status

Trial start date: 1^th^ July 2014; Currently recruiting (N_current_ = 80 as of March 17, 2016).

## Abbreviations

AAQ: Acceptance and action questionnaire
ANCOVA: Analysis of covariance
BDI: Beck depression inventory
CSQ: Client satisfaction questionnaire
DT: Distress thermometer
FACIT-F: German Version Functional Assessment of Chronic Illness Therapy-Fatigue
FACT (−F): Functional Assessment of Cancer Therapy including Fatigue
FAH II: Fragebogen zur Akzeptanz und Handeln
HADS: Hospital anxiety and depression scale
LOCF: Last observation carried forward
RCT: Randomized controlled trial
STREAM: STREss Aktiv Mindern
SUS: System usability scale
WAI-SR: Short version working alliance inventory
ZUF-8: Fragebogen zur Messung der Patientenzufriedenheit
